#### **8.4 Database Lock**

Prior to database lock, the Trial Manager will review any outstanding warnings on the eCRF and resolve or close these as appropriate before database lock. Local study personnel should resolve any queries that arise promptly. Once all queries have been resolved no further changes will be made to the database unless specifically requested by the Study Office in response to the Statistician's data checks. The study Chief Investigator will review all the data and provide electronic signature to verify that all the data are complete and correct. At this point, all data will be formally locked for analysis.

#### **8.5 Archiving**

Chief Investigator will be responsible for securely archiving local data generated, essential documents and source data in accordance with local requirements, but for at least 5 years from the end of the study.

## **9 Statistical Considerations**

### **9.1 Sample Size Calculation**

A two-sided log-rank test with an overall sample size of 1314 subjects (657 in the deferred vaccination group and 657 in the prompt vaccination group) achieves 80.0% power at a 0.050 significance level to detect a hazard ratio of 1.5 when the proportion surviving (no occurrence of symptomatic uveitis worsening) in the deferred vaccination group is 0.9000. The study lasts for 6 time periods of which subject accrual (entry) occurs in the first 3 time periods. The accrual pattern across time periods is uniform (all periods equal). The proportion dropping out of both groups is 0.1500, respectively.

### **9.2 Data Analyses**

Analysis methods of each study outcome will be provided in a detailed statistical analysis plan.

Primary analyses will be on an Intention-to-treat (ITT) basis. According to the intention-to-treat principle (ITT), all patients who have been randomized regardless of their compliance with the study intervention and whose primary outcome is available will be included, which is one of the main data sets for the effectiveness evaluation of this study. Given the pragmatic nature of the trial and the expected gaps in data on patient compliance with randomized intervention, we will not consider the per-protocol (PP) analysis as the primary analysis.

The clinical and demographic characteristics of the participants will be summarized with descriptive statistics. Continuous variables will be described with their distribution range, mean, median, standard deviation, and interquartile range, as appropriate. Categorical variables will be summarized as numbers and the proportions.

The primary outcome will be the time to symptomatic uveitis worsening. For the primary outcome, the multiplicative limit method (Kaplan-Meier) is used for univariate survival analysis, the median time to symptomatic uveitis worsening and survival rate of each group are calculated, and the survival rate curve is compared by the Log-rank test.

For the systemic outcomes, the types, number, and incidence of all systemic adverse events during the follow-up period will be described in a tabular form.

### **9.3 Interim Analysis**

This study does not plan to perform interim analysis.

## **10 Ethical Considerations**

This clinical trial will be conducted in compliance with the approved protocol, the Helsinki Declaration, the Drug Clinical trial Management Code issued by the CFDA, and corresponding regulations.

Before the commencement of this experiment, the approval of the ethics committee must be obtained.

The Investigator is expected to take any immediate action required for the safety of any patient included in this study, even if this action represents a deviation from the protocol.

During the clinical study, any changes made to this trial protocol should be reported to the Ethics Committee and placed on record.

Subjects must provide informed consent to participate in the trial.

If the subject and his or her legal representative are illiterate, the informed consent process shall be attended by a witness, who shall sign the informed consent form after oral consent by the subject or his or her legitimate representative.

A copy of the informed consent form and the contact information for the researcher and the ethics committee must be provided to the patient.

The study site must be equipped with the necessary medical rescue equipment and first aid drugs for emergency issues.

## Appendix I

### SUN Working Group Grading System for Anterior Chamber Cells

| Grade | Number of cells in field a |
|-------|---------------------------------------|
| 0     | <1                                    |
| 0.5+  | 1-5                                   |
| 1+    | 6-15                                  |
| 2+    | 16-25                                 |
| 3+    | 26-50                                 |
| 4+    | >50                                   |

a Field size is a 1mm by 1mm slit lamp beam. Grading should be done with the highest magnification and illumination and conducted in a completely dark room, prior to dilation.

From Jabs DA et al. Standardization of uveitis nomenclature for reporting clinical data. Results of the First International Workshop. Am J Ophthalmol 2005;140(3):509-16.

## Appendix II

### National Eye Institute (NEI)/SUN Criteria for Grading Vitreous Haze

| Grade | Description a                                                                                                                 |
|-------|------------------------------------------------------------------------------------------------------------------------------------------|
| 0     | No evident vitreal haze                                                                                                                  |
| 0.5+  | Slight blurring of the optic disc margin because of the haze; normal striations and reflex of the nerve fiber layer cannot be visualized |
| 1+    | Permits a better definition of both the optic nerve head and the retinal vessels (compared to higher grades)                             |
| 2+    | Permits better visualization of the retinal vessels (compared to higher grades)                                                          |
| 3+    | Permits the observer to see the optic nerve head, but the borders are quite blurry                                                       |
| 4+    | Optic nerve head is obscured                                                                                                             |

a Grading should be conducted in a completely dark room.

[figure not shown]

From Nussenblatt et al. Standardization of vitreal inflammatory activity in intermediate and posterior uveitis. Ophthalmology 1985;92:467-471.

# **1 Introduction**

This is an investigator-initiated, parallel group-randomized, pragmatic trial to test the difference in ocular and systemic outcomes between prompt initiation of COVID-19 vaccination and deferred initiation of COVID-19 vaccination in patients with uveitis.

Approximately 1314 eligible subjects will be randomized 1:1 (657 subjects per group) to receive one of two vaccination strategy recommendations. In the prompt vaccination arm, subjects will be recommended to get a prompt initiation of COVID-19 vaccination. In the deferred vaccination arm, subjects will be recommended to get the vaccination after uveitis remission (inactive disease for 3 months after discontinuing all treatments for eye disease). All participants will be followed up for 3 months since randomization. The primary outcome will be the difference in time to symptomatic uveitis worsening.

The statistical analysis plan (SAP) documents the planned statistical analyses for the trial and is based on the protocol, together with any subsequent amendments. The SAP is intended for the use of project team members and should be read in conjunction with the aforementioned protocol. The analyses that are detailed in this SAP will be performed only when the database has been locked and all protocol violators identified. Analysis populations will be determined using the rules prespecified in this SAP. At a date to be agreed within the project team, a data look and further analysis will be performed.

## **2 Study Objective**

### **2.1 Primary Objective**

To compare the time to symptomatic uveitis worsening between prompt and deferred vaccination strategies for patients with uveitis.

## **2.2 Secondary Objectives**

To compare vaccine accessibility, patient compliance, clinically-confirmed uveitis worsening, visual outcomes, treatment interruptions and initiation of step-up treatment, hospitalization, laboratory-confirmed COVID-19 between prompt and deferred vaccination strategies for patients with uveitis.

## **2.3 Safety Objectives**

To evaluate the systemic adverse events of the prompt versus deferred vaccination strategies for patients with uveitis.

# **3 Study Outcomes**

## **3.1 Primary Outcome**

An adjudication committee who are unaware of group assignment will independently determine each endpoint event according to telephone call records from the call center, medical data, records and examination reports written by the follow-up staff, the primary treating ophthalmologist, the attending doctor or the examining doctor. These medical notes and data will be collected by a group of Study Coordinators who mask any randomization assignment information and submit these materials to the adjudication committee.

The primary outcome will be the time to symptomatic worsening over the course of 3 months of follow-up.

Symptomatic worsening is defined if one of following newly onset symptoms occurs in at least one eye lasting for at least 2 days: eye redness, eye pain, decreased vision, light sensitivity or floaters.

## **3.2 Secondary and Safety Outcomes**

- a. Time to clinically-confirmed uveitis worsening.

Clinically-confirmed uveitis worsening is defined if any of the following criteria are met in at least one eye: new active, inflammatory chorioretinal or retinal vascular lesions (determined by clinical examination such as ophthalmoscopy or ancillary testing such as fundus photography and fluorescein angiography); worsening of best corrected visual acuity by 0.3 LogMAR score or more; a two-step increase in anterior chamber cell grade relative to baseline; or a two-step increase in vitreous haze grade relative to baseline. *A 2-step increase is represented by a change of grade 0 to grade 2+; or grade 0.5+ to grade 3+.*

- b. Proportion of each reason for symptomatic uveitis worsening.
- c. Proportion of symptomatic uveitis worsening.
- d. Proportion of each reason for clinically-confirmed uveitis worsening.
- e. Time to initiation of step-up treatment.

Step-up treatment is defined if any of the following criteria are met: addition of another systemic immunosuppressive agent (or biologics), switching to another systemic immunosuppressive agent (or biologics), or increasing doses of any currently systemically administered drugs.

- f. Time to treatment interruptions.

Treatment interruptions are defined if any of the following criteria are met: decreasing doses of or discontinuing any currently systemically administered drugs due to adverse events rather than disease improvement.

- g. Time to hospitalization for any reasons.
- h. Time to hospitalization for ocular disease.
- i. Time to laboratory-confirmed COVID-19.
- j. Patient adherence, defined as proportion correctly vaccinated for at least one dose or maintaining not vaccinated per protocol throughout the trial.

k. Proportion of vaccinated type and dose.

l. Proportion of uveitis remission throughout the trial.

Uveitis remission is defined as an inactive disease for 3 months after discontinuing all treatments for eye disease.

m. Vaccine inaccessibility, defined as proportion having gone to the vaccination site but refused due to the lack of vaccines, whereby this situation continues until the end of trial.

n. Reasons for not yet vaccinated until the end of trial among those who should have been vaccinated per protocol.

o. Change in anterior chamber cells from the Baseline to the end of three months.

p. Change in vitreous haze from the Baseline to the end of three months.

q. Change in best corrected visual acuity LogMAR score from the Baseline to the end of three months.

r. Incidence of any systemic adverse event (apart from uveitis related events).

## **4 Statistical Hypothesis**

There is one formal comparison of interest on primary outcome:

Prompt vaccination strategy vs. Deferred vaccination strategy

Prompt vaccination strategy is hypothesized to result in an earlier occurrence of primary endpoint event as compared with deferred vaccination strategy.

The null hypothesis, that prompt vaccination strategy does not result in an earlier occurrence of primary endpoint event, will be rejected if the estimated 95% confidence interval for the hazard ratio of prompt vaccination strategy lies wholly above 1.

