## **2 Objectives**

### **2.1 Trial Objectives**

The objective is to test the difference in ocular and systemic outcomes between prompt initiation of COVID-19 vaccination and deferred initiation of COVID-19 vaccination in patients with uveitis.

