## **5 Sample Size**

A two-sided log-rank test with an overall sample size of 1314 subjects (657 in the deferred vaccination group and 657 in the prompt vaccination group) achieves 80.0% power at a 0.050 significance level to detect a hazard ratio of 1.5 when the proportion surviving (no occurrence of symptomatic uveitis worsening) in the deferred vaccination group is 0.9000. The study lasts for 6 time periods of which subject accrual (entry) occurs in the first 3 time periods. The accrual pattern across time periods is uniform (all periods equal). The proportion dropping out of both groups is 0.1500, respectively.

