## **10 Primary Outcome Comparison**

The primary outcome, time to uveitis symptomatic worsening over the course of 3 months of follow-up, will be compared with the Log-rank test. If a participant does not experience the primary endpoint event, they will have their data censored at the encounter where withdrawal or loss to follow-up occurs, or the final (month 3) follow-up encounter (whichever is earlier). For those with primary endpoint event, the censoring time point will be at the specific telephone call encounter (month 1, month 2, or month 3) where the occurrence of primary endpoint event is reported. Follow-up data after month 3 will no longer be included in the analysis, if any. The multiplicative limit method (Kaplan-Meier) will be used to show the cumulative incidence of primary endpoint event. A proportional hazard model (univariate Cox regression) is used to calculate the hazard ratio as well as 95% CI. The proportional-hazards assumption will be checked by means of inspection of a log-log survival plot.

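### SAP 4 decides the primary comparison by a one-directional rule at about 2.5%, the sample size rests on a two-sided 5% log-rank test, and the documents do not say which one decides

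*Supplement*

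**What the plan says.** SAP section 4 names one formal comparison, prompt against deferred vaccination, and expects earlier events under prompt vaccination. It frames the null in one direction: "The null hypothesis, that prompt vaccination strategy does not result in an earlier occurrence of primary endpoint event". That null "will be rejected if the estimated 95% confidence interval for the hazard ratio of prompt vaccination strategy lies wholly above 1". Nothing is said about an interval wholly below 1.

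SAP section 5, which repeats protocol section 9.1, bases the size of the trial on another test: "A two-sided log-rank test with an overall sample size of 1314 subjects", which "achieves 80.0% power at a 0.050 significance level to detect a hazard ratio of 1.5".

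SAP section 10 says that the primary outcome "will be compared with the Log-rank test" and takes the hazard ratio and its 95% interval from a univariate Cox model. It gives no sidedness, no significance level and no rejection threshold. Protocol section 9.2 likewise compares the curves by the log-rank test.

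The protocol's question has no direction. Section 2.1 reads: "The objective is to test the difference in ocular and systemic outcomes". The key question in section 1.1 is also whether outcomes differ between the strategies.

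**The concern.** The trial has one confirmatory comparison, and SAP section 11.1 rules out inference on secondary outcomes. The formal conclusion therefore depends on the decision rule for that comparison. SAP 4 supplies a rule that can reject only when prompt vaccination looks worse. SAP 5, SAP 10 and the protocol point to a two-sided test of any difference.

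If prompt vaccination were associated with later or fewer worsenings, the log-rank test could be significant while the SAP 4 null stayed unrejected. The protocol's question would then have no formal answer in that direction, and the SAP does not rank the two results. The two-sided 0.050 level quoted with the sample size also does not describe the SAP 4 rule.

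**Working it through.** **Inputs.** From SAP 5: 657 per arm, hazard ratio 1.5, power 80%, two-sided 0.050, deferred arm 0.90 event-free, 6 periods with uniform entry over the first 3, dropout 0.15. From SAP 10: event times placed at months 1, 2 and 3. Assumptions: 0.90 applies at month 3 (SAP 5 gives no time point), and the 15% loss is spread over three months.

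**1. The plan's own figure.**
- Freedman events: (1.96 + 0.8416)² × ((1 + 1.5)/(1 − 1.5))² = 7.849 × 25 = 196.2, so 197.
- With follow-up of 3 to 6 periods, the event probability is 0.146 (deferred) and 0.210 (prompt), mean 0.178.
- 197/0.178 = 1107, and 1107/0.85 = 1302, within 1% of 1314.
- The same route for a one-sided 5% test needs 155 events and about 1024 participants. The stated 1314 therefore fits a two-sided 5% test, which has the same critical value as a one-sided 2.5% test.

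**2. The two rules under the normal approximation.** With E events, the standardised log hazard ratio has mean (√E/2) × ln(HR). Schoenfeld's formula gives E = 4 × 7.849/(ln 1.5)² = 191, so the mean at HR 1.5 is 6.910 × 0.4055 = 2.80.

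| True HR | SAP 4 rule rejects | Two-sided log-rank rejects |
|---|---|---|
| 1 | 0.025 | 0.050 |
| 1.5 | Φ(2.80 − 1.96) = 0.800 | 0.800 |
| 0.667 | Φ(−2.80 − 1.96) = 0.000 | 0.800 |

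**3. Three months of follow-up for everyone.** At HR 0.667 the event probabilities are 0.100 and 1 − 0.9^(2/3) = 0.068, mean 0.084.
- No loss: 1314 × 0.0839 = 110 events; Φ(5.25 × 0.4055 − 1.96) = 0.57.
- All 15% lost without contributing: 94 events; Φ(4.84 × 0.4055 − 1.96) = 0.50.

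A log-rank rejection rate between 50% and 57% is therefore expected.

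**4. Simulation.** Three sets were run, two of 20,000 and one of 8,000 trials per scenario, with 657 per arm and events grouped at months 1 to 3. The Cox interval used Breslow or Efron handling of ties, because the SAP names no method.

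| True HR | Log-rank rejects | SAP 4 rule rejects | Verdicts differ |
|---|---|---|---|
| 1 | 4.7% to 5.1% | 1.9% to 2.3% | 2.7% to 2.9%, nearly all with prompt better |
| 1.5 | see below | see below | 0.3% to 0.4% (Efron), 1.7% to 1.9% (Breslow) |
| 0.67 | 51% to 55% | none | every log-rank rejection |

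At HR 1.5 with Breslow ties, one set gave 67.9% for the log-rank test and 66.1% for the SAP 4 rule. Both lie below 80% because everyone is followed for only three months, a separate matter that affects both rules alike. The gap between the rules is the part that belongs to this point.

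**The case against.** A directional hypothesis is a legitimate choice. The protocol names relapse as the main risk, SAP 4 expects harm, and its rule is stricter than a two-sided 5% test, so false positives are not inflated. If prompt vaccination is truly better, the SAP 4 null is true and not rejecting it is correct; a significant log-rank result can stand beside it without logical contradiction. The Cox interval would be reported in any case, so an interval below 1 would be visible. Bringing SAP 5 and the protocol wording into line with SAP 4 would be equally coherent.

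Much of this stands, and it rules out several stronger readings that a reader might infer:
- *That SAP 10 itself prescribes a two-sided 5% test.* It names only the log-rank test; sidedness and level come from SAP 5 and protocol 9.1.
- *That power or sample size is wrong because of the SAP 4 rule.* In the harm direction both rules use 1.96, and power at HR 1.5 is 0.800 under each at 191 events.
- *That verdicts on harm often conflict.* They differ only in borderline data, and the larger figure needs Breslow ties.
- *That the choice of rule is left open until the data are seen.* SAP 4 does pre-specify a rejection rule. The gap is that its precedence over the log-rank test is not stated.

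The mismatch itself remains. A reported interval does not say whether a difference has been formally concluded. For hazard ratios below 1, SAP 4 and a two-sided log-rank test give different answers to the protocol's question.

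**Conclusion.** The concern holds in a limited form. SAP 4 applies a one-directional rule at about 2.5%, the sample size and the protocol's question are two-sided, and no section says whether the Cox interval or the log-rank test decides.

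The material consequence is confined to effects favouring prompt vaccination. There SAP 4 can never reject, while the log-rank test at HR 0.67 would do so in about 51% to 55% of trials. That figure assumes 0.90 event-free at month 3, 15% loss over three months and monthly event times; with the 191 events behind the stated power it would be 80%. On the harm side the effect is about 0.3% to 1.9% of trials at HR 1.5, depending on an unstated tie method. Sample size and power for the planned effect are essentially untouched.

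**What to change.** In SAP 4, state that the null is a hazard ratio of 1, tested two-sided, and that the decision rests on the two-sided log-rank test at 0.05 on which the sample size was based. Keep the Cox hazard ratio with its 95% interval as the estimate that gives size and direction, and keep earlier worsening under prompt vaccination as the expected direction. Repeat the sidedness and level in SAP 10 so that the sections agree. The tie method for the Cox model can be named in the same edit; it would then affect only the estimate and not the decision.

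The cost is a few sentences, but the change is not free. The directional null is given up, and total type I error becomes the stated 5% instead of 2.5%. The sample size of 1314, the required events (191 by Schoenfeld, 197 by Freedman) and the power at HR 1.5 do not change.

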## **5 Sample Size**

A two-sided log-rank test with an overall sample size of 1314 subjects (657 in the deferred vaccination group and 657 in the prompt vaccination group) achieves 80.0% power at a 0.050 significance level to detect a hazard ratio of 1.5 when the proportion surviving (no occurrence of symptomatic uveitis worsening) in the deferred vaccination group is 0.9000. The study lasts for 6 time periods of which subject accrual (entry) occurs in the first 3 time periods. The accrual pattern across time periods is uniform (all periods equal). The proportion dropping out of both groups is 0.1500, respectively.

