### 3 Study Design

#### 3.1 Overall Design

This is a pragmatic, randomized clinical trial to test the difference in ocular and systemic outcomes between prompt initiation of COVID-19 vaccination and deferred initiation of COVID-19 vaccination in uveitis patients who have not yet been vaccinated and whose ocular disease maintains inactive but has not yet achieved complete remission.

Approximately 1314 eligible subjects will be randomized 1:1 (657 subjects per group) to receive one of two vaccination strategy recommendations. In the prompt vaccination arm, subjects will be recommended to get a prompt initiation of COVID-19 vaccination. In the deferred vaccination arm, subjects will be recommended to get the vaccination after uveitis remission (inactive disease for 3 months after discontinuing all treatments for eye disease). All participants will be followed up for 3 months since randomization. The primary outcome will be the difference in time to symptomatic uveitis worsening.

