## **9 Statistical Considerations**

### **9.1 Sample Size Calculation**

A two-sided log-rank test with an overall sample size of 1314 subjects (657 in the deferred vaccination group and 657 in the prompt vaccination group) achieves 80.0% power at a 0.050 significance level to detect a hazard ratio of 1.5 when the proportion surviving (no occurrence of symptomatic uveitis worsening) in the deferred vaccination group is 0.9000. The study lasts for 6 time periods of which subject accrual (entry) occurs in the first 3 time periods. The accrual pattern across time periods is uniform (all periods equal). The proportion dropping out of both groups is 0.1500, respectively.

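### The sample size credits 3 to 6 months of follow-up, but only 3 months per participant are analysed, so 1314 patients give about 65-73% power for HR 1.5 rather than 80% if 0.90 is the month-3 event-free proportion

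*Supplement*

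**What the plan says.** The sample size paragraph is the same in SAP section 5 and protocol 9.1. It says that 1314 subjects, 657 per arm, give a two-sided log-rank test that "achieves 80.0% power at a 0.050 significance level to detect a hazard ratio of 1.5". The other inputs are:

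- **Control arm:** "the proportion surviving (no occurrence of symptomatic uveitis worsening) in the deferred vaccination group is 0.9000". No time point is attached.
- **Duration:** "The study lasts for 6 time periods of which subject accrual (entry) occurs in the first 3 time periods", with uniform entry.
- **Dropout:** "The proportion dropping out of both groups is 0.1500, respectively". No period is attached.

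Protocol 3.3 puts the start in July 2021, the end of enrolment in October 2021 and the end of the trial in January 2022. Three periods of entry and six in total therefore match calendar months.

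The follow-up that is analysed is shorter. Protocol 3.1 and SAP section 1 say: "All participants will be followed up for 3 months since randomization". Protocol 6.2 and SAP 3.1 define the primary outcome over 3 months. SAP section 10 censors at the month 3 encounter and adds: "Follow-up data after month 3 will no longer be included in the analysis, if any".

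**The concern.** In an accrual-plus-follow-up log-rank calculation, someone who enters at the start is at risk until the study closes, and someone who enters last is at risk for the remaining 3 periods. That suits a trial with a common closing date. Here each participant's clock stops at month 3 whatever the entry date, so the calendar length of the trial has been used as time at risk.

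The single formal hypothesis (SAP section 4) is that prompt vaccination brings earlier worsening, which is a question of harm. If the confidence interval for the hazard ratio does not lie wholly above 1, readers will weigh that result against a stated 80% power. With power of 65-70%, the chance of missing a true hazard ratio of 1.5 is 30-35%, not 20%.

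**Working it through.** **Inputs from the documents:** 657 per arm, HR 1.5, two-sided alpha 0.05, 80% power, 0.90 event-free in the deferred arm, uniform entry over 3 of 6 months, 15% dropout, analysis stopped at month 3. **Assumptions:** exponential event times; 0.90 applies at month 3; dropout handled in several ways, because its period is not given.

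**1. Hazards.** Deferred: -ln(0.90)/3 = 0.03512 per month. Prompt: 1.5 × 0.03512 = 0.05268.

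**2. Events needed for 80% power.**
- Schoenfeld: 4(1.960 + 0.842)²/(ln 1.5)² = 191.
- Freedman: (1.960 + 0.842)² × (2.5/0.5)² = 197 after rounding up.

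**3. The plan's own figure.** With follow-up spread evenly over 3 to 6 months, the event probability is 1 - (e^(-3h) - e^(-6h))/(3h).
- Deferred: 1 - (0.900 - 0.810)/0.1054 = 0.146. Prompt: 1 - (0.8538 - 0.7290)/0.1580 = 0.210. Average: 0.178.
- Required N with dropout as N/(1 - 0.15): Freedman 197/0.1780/0.85 = 1302; Schoenfeld 191/0.1780/0.85 = 1262; a Lakatos-type calculation gives 1288. The plan states 1314.
- Power at 1314: 1314 × 0.85 × 0.1780 = 199 events, giving 80.5% (Freedman), 80.8% (Lakatos) and 81.6% (Schoenfeld).

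The stated figures are approximately recovered when months 4 to 6 are counted. A fixed 3-month follow-up with the same 0.90 needs 1552-1600 without dropout and 1826-1883 with N/(1 - 0.15).

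**4. The analysis as planned: everyone stops at month 3, N = 1314.** Without loss the event probabilities are 0.1000 and 1 - 0.9^1.5 = 0.1462. For gradual loss of 15% by month 3, the dropout hazard is g = -ln(0.85)/3 = 0.0542, and h/(h + g) × (1 - e^(-3(h + g))) gives 0.0924 and 0.1352. Schoenfeld power is Φ(√D × ln(1.5)/2 - 1.960), where D is the number of events.

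| Dropout handling | Events | Power (Freedman, Lakatos, Schoenfeld) |
|---|---|---|
| None | 657 × (0.1000 + 0.1462) = 162 | 72-73% |
| 15% lost gradually by month 3 | 657 × (0.0924 + 0.1352) = 150 | 68.6%, 68.9%, 69.8% |
| 15% removed at the outset | 161.7 × 0.85 = 137 | 65-66% |
| 15% per month | 129 | 62-63% |

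A simulation with event times grouped at the monthly calls, as SAP section 10 specifies, agrees: 72.9% without loss, 69.0% with gradual loss, and 65.7% with 15% removed at the outset. With gradual loss it falls to 66.9% if an event counts only when the next call is reached.

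**5. If 0.90 belongs to another time point (fixed 3-month analysis).**
- Month 6: power about 42-45%.
- Month 2: 84% with 15% lost by month 3, 87% with no loss.
- Power is exactly 80% at about month 2.25 with 15% lost by month 3, and at about month 2.45 with no loss.

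**6. Detectable effect.** With 0.90 at month 3 and 15% lost by month 3, 1314 patients give 80% power for a hazard ratio of about 1.57.

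**The case against.** The strongest objection is that the sponsor's actual software inputs are unknown. Neither the horizon of the 0.90 nor the period of the 15% is given, and no variant tried returns exactly 1314. The variant that comes closest removes 15% outright, which gives 65-66% at 3 months; 69-70% comes from gradual loss, which fits the censoring in SAP section 10. A reader might infer that the power simply is 70%. The documents do not support one number, only a range that depends on these two inputs.

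The mismatch itself does not depend on them. Suppose the horizon of the 0.90 is tuned so that the 6-period calculation returns exactly 80% at 1314. The tuned horizon is month 2.53, 3.22 or 3.43 with 15% lost per 1, 3 or 6 months, and the fixed 3-month power is then 69%, 66% or 65%.

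The protocol's schedule (5.10) lists a phone call after Month 3 with the symptom questions, so some later data may exist. This does not rescue the calculation, because the outcome is defined over 3 months and SAP section 10 excludes those data.

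The correction also leaves the estimand, test, analysis set and error rate unchanged, and the final confidence interval will show the precision reached. That stands. It limits the harm to the planning statement and to how a null result is read.

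**Conclusion.** The sample size paragraph and the primary analysis describe different follow-up, and nothing in either document reconciles them. If 0.90 is the month-3 event-free proportion, the planned analysis yields about 137-162 events against the 191-197 needed, and power for HR 1.5 is about 65-73%: about 69-70% with 15% lost gradually by month 3, and about 62% if the 15% is per month. Month 3 is an assumption. It is supported by the outcome's own horizon and by coming closest to 1314: in the 6-period calculation, 0.90 at month 6 would call for roughly 2,000 patients or more, and 0.90 at month 2 for no more than 1065. The 80% claim would hold only if 0.90 applied at about month 2.25 (15% lost by month 3) to 2.45 (no loss) or earlier, and no passage suggests that.

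Two stronger readings fail. The calculation does not credit everyone with 6 months; it credits 3 to 6. Nor does the shortfall show that 1314 must be raised: the trial can keep its size if it states the power that this size provides.

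**What to change.** In SAP section 5 and protocol 9.1:

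1. Replace the 6-period design with a fixed 3-month follow-up per participant.
2. State the time point to which the 0.90 refers and the period over which 15% drop out. The sponsor has to supply both.
3. Restate expected events and power from those inputs. With 0.90 at month 3 and 15% lost by month 3, the text would read: about 150 events, about 70% power for HR 1.5, and 80% power for HR of about 1.57.
4. Keep 1314.

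The cost is one rewritten paragraph in each document and a less favourable stated power. No extra patients, visits or changes to the analysis are needed.
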